**Fig. 1 Fig1:**
[figure not shown]
Describes the participant flow through the various activities of the study

The study will be conducted through a partnership between Johns Hopkins Center for American Indian Health (JHU) and a tribal community residing on a reservation in rural Arizona. The trial design and study protocol were reviewed and approved by the Tribe’s governing Tribal Council and Health Advisory Board as well as the JHU and IHS research review boards. This manuscript was reviewed and approved by the Tribal Council and Health Advisory Board. Any serious adverse event reported or detected during the trial will be documented and reported to the relevant research review boards within 24 h. There is no Data and Safety Monitoring Board for this trial. (Note: a completed SPIRIT checklist was submitted along with the manuscript to the journal).

### Participant recruitment and informed consent

To participate in the study participants must meet the following criteria: Native American ethnicity, 14–26 years of age, member of the participating tribal community, written informed consent, had vaginal or anal sex at least once in their lifetime, and be in possession of their own cell phone. We will utilize a non-probability sampling frame that includes posting flyers in public and conducting in-person recruitment at community gathering locations. Study staff will screen potential participants for eligibility criteria. If eligible and interested, individuals will complete informed consent. Note: The relevant Institutional Review Boards (IRB) approved for minors ages 14–17 to consent to study participation as adults in lieu of requiring parental permission. This decision is based on state law allowing individuals ages 14 and older to consent to STI screening without parental permission. Thus, the IRBs believed requiring parental permission could potentially act as a barrier to study participation and preclude access to the benefit of STI screening. The first participant was recruited on April 1, 2019.

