## Background

Disparities in sexually transmitted infections (STI) are an urgent problem among Native American (Native) youth and young adults. Nationwide, in 2017, the Chlamydia rate among Native Americans was 47.7% higher than the general population (781.2/100,000 vs. 528.8/1000) and rates of Chlamydia rose 3.7% among Natives between 2013 and 2017 [1]. Further, Natives had the second highest Gonorrhea rate among all races/ethnicities in 2017 [1].

Native young adults and adolescents suffer from high rates of Gonorrhea, with a rate of 561.9/100,000 for those between ages 15–19, and 926.6/100,000 for those between ages 20–24; these rates are 4.2 and 3.6 times the rate among Whites, respectively [1]. In 2013, in Arizona, where this study will take place, Native American females ages 20–24 endured the highest rates of Chlamydia among any demographic in Arizona, at 7767/100,000, which is 1.5 times the rate for Native females of the same age nationwide (5310/100,000) [2]. Additionally in Arizona, from 2012 to 2013 the greatest increase in Gonorrhea rates were among Native Americans (23%) [2].

Research attempting to explain this gap in STIs indicates a higher prevalence of STIs among Native youth and young adults is not fully explained by different sexual or substance use behaviors [3]. These disparities in sexual health by ethnicity may be better attributed to social environments and structural determinants such as a shortage of sexual healthcare providers, socioeconomic status, and access barriers to healthcare including confidentiality concerns, and geographic isolation [4–10]. Further, because many STIs can be treated free of charge within the Indian Health Service (IHS), differential access to screening and treatment may explain these disparities [3]. Data from IHS corroborate inequalities in access to care, namely underutilization of services by higher risk groups and a lack of universal promotion of sexual health care by providers [4, 11].

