### Study aims

This study will be conducted in the southwestern U.S. with Native American youth and young adults (ages 14–26) residing in a rural, reservation-based community. We will conduct a two-arm randomized controlled trial to evaluate the POFG program for impacts on STI screening uptake, sexual health risk behaviors and protective sexual health practices. The primary research questions include: 1) Does POFG increase STI screening uptake; 2) Does POFG increase condom use at last sex; and 3) Does POFG decrease number of new sexual partners. Secondary research questions include exploring what participant variables impact the primary outcome of STI screening uptake, including: 1) sexual health knowledge, efficacy and intentions; 2) substance use; 3) psychosocial assets and resources; and 4) experiencing past symptoms of a STI.

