### Participant randomization and study sample size

This study is at RCT. The randomization sequence is computer generated and used to randomize individuals to one of two study groups: intervention or control. A stratified randomization technique will be used to ensure equivalent 1:1 allocation of study conditions across three gender groups (male/trans male; female/trans female and other, which includes those who identify as two-spirited, bi-gendered, crossdresser, genderqueer, or for whom none of these options apply), and three age groups (i.e. 14–17, 18–21, and 22–26). Within each age/gender strata, participants will be randomized in blocks of 4 to ensure equal allocation to intervention and control groups. Participants, but not study staff or investigators, will be blinded to study group participation.

The primary outcome is completion of self-administered STI screening between the baseline and 3-month study visit. Based on prior research, we estimate that 20–25% of the control group will complete STI screening [12]. We anticipate POFG will increase STI screening by at least 50% (i.e. relative risk of 1.5 comparing the proportion completing STI screening in the intervention group to the control group). Given these assumptions, retention rates from past RCTs conducted by the study team within the target population, a two-sided alpha of 0.05 and 80% power, we will enroll a total of 450 participants (225 in each arm) to sufficiently power the trial.

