### Study visits and data collection

Data will be collected at baseline, 3 months, and 6 months post-intervention completion. At each study visit, participants will complete the aforementioned surveys. Data will be collected via tablets using REDcap (Research Electronic Data Capture) electronic data capture tools hosted at JHU [29]. REDCap is a secure, web-based application designed to support data capture for research studies, providing 1) an intuitive interface for validated data entry; 2) audit trails for tracking data manipulation and export procedures; 3) automated export procedures for seamless data downloads to common statistical packages; and 4) procedures for importing data from external sources. Participants will receive $30, $30 and $45 gift cards after completion of the baseline, 3- and 6-month post-intervention evaluations, respectively.

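### Baseline STI screening has no fixed role in the primary analysis: adjustment waits on observed imbalance, and moderation analysis waits on a positive result

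*Protocol article*

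**What the plan says.** **Eligibility** (Participant recruitment and informed consent). The list of conditions begins: "To participate in the study participants must meet the following criteria: Native American ethnicity, 14–26 years of age, member of the participating tribal community". The remaining conditions are written consent, lifetime sexual experience and owning a cell phone. None concerns time since the last STI test or treatment.

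**Rationale** (Background): access to care is described as unequal, with "underutilization of services by higher risk groups and a lack of universal promotion of sexual health care by providers".

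**Data collected** (Measures; Study visits and data collection): the two self-report surveys cover STI screening uptake and STI history. "At each study visit, participants will complete the aforementioned surveys", so both topics are covered at baseline.

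**Analysis** (Statistical analysis): the primary outcome is return of a study kit by 3 months. It is compared by chi-square test, or by log-binomial regression if the arms are seen to differ at baseline. Mediation and moderation analyses follow only if efficacy appears at 3 or 6 months.

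**Variables to explore** (Study aims): the secondary questions concern "exploring what participant variables impact the primary outcome of STI screening uptake". Those named are knowledge, efficacy and intention measures; substance use; assets and resources; and earlier STI symptoms. Prior screening is not among them.

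**The concern.** Someone tested at a clinic shortly before enrolment may reasonably decline another test and is then counted as not screened. Whether a participant was recently screened is a plausible predictor of kit return and a plausible modifier of the intervention's effect. Recruitment by flyers and at gathering places leaves the share of such volunteers uncontrolled, and randomisation is stratified by gender and age only.

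The plan collects this information but lets two results decide whether it is used. Choosing between an unadjusted and an adjusted primary analysis after looking at baseline balance leaves the primary method open until the data are seen. Imbalance is also a poor guide to which covariates are worth including, because the precision gain comes from how strongly a covariate predicts the outcome. Making moderation conditional on efficacy removes it after a null result, when readers would most want to know whether people with no screening gap masked an effect in the others.

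**Working it through.** **Inputs from the protocol** (Participant randomization and study sample size): "a two-sided alpha of 0.05 and 80% power"; "we estimate that 20–25% of the control group will complete STI screening"; "relative risk of 1.5 comparing the proportion completing STI screening in the intervention group to the control group"; 225 per arm. Retention is mentioned without a figure, so no loss is assumed below.

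**Formula.** For control and intervention rates pC and pI, mean p̄, difference d and n per arm:

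power = Φ{[d√n − 1.96·√(2p̄(1−p̄))] / √(pC(1−pC) + pI(1−pI))}

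**Step 1: the plan's own figure.**
- 25% vs 37.5%: 215 per arm (430 in total). At n = 225, (0.125 × 15 − 1.96 × 0.6555) / 0.6495 = 0.909, so power is 81.8%. The planned 450 reproduces here, with room for 1 − 215/225 = 4.4% loss.
- 20% vs 30%: 294 per arm (588 in total), and power at 225 is 68.9%. The planned 450 does not reproduce at this end of the range.

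**Step 2: a dilution scenario.** Three inputs are assumptions that the documents do not give: a share r was recently screened, 10% of that share return a kit in either arm, and the rest follow 25% vs 37.5%. Pooled rate = (1 − r) × rate in the rest + r × 0.10.

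**Step 3: adjusting for recent screening.** The difference is the same, d = (1 − r) × 0.125, but both variance terms become within-stratum averages:
- null: (1 − r) × 2(0.3125)(0.6875) + r × 2(0.10)(0.90)
- alternative: (1 − r) × [0.25(0.75) + 0.375(0.625)] + r × 2(0.10)(0.90)

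| r | Pooled rates | Difference (points) | RR | Power, unadjusted | Power, stratified |
|---|---|---|---|---|---|
| 0 | 25.0% vs 37.5% | 12.5 | 1.50 | 81.8% | 81.8% |
| 10% | 23.5% vs 34.75% | 11.25 | 1.48 | 74.9% | 75.8% |
| 20% | 22.0% vs 32.0% | 10.0 | 1.45 | 66.7% | 68.4% |
| 30% | 20.5% vs 29.25% | 8.75 | 1.43 | 57.5% | 59.7% |

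Worked line for r = 20%:
- Unadjusted: (0.100 × 15 − 1.96 × 0.6279) / 0.6239 = 0.432, giving 66.7%.
- Stratified: the null variance is 0.8 × 0.4297 + 0.2 × 0.18 = 0.3798 and the alternative is 0.8 × 0.4219 + 0.2 × 0.18 = 0.3735. Then (1.5 − 1.96 × 0.6163) / 0.6111 = 0.478, giving 68.4%.

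Adjustment recovers 0.9, 1.7 and 2.2 points.

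**Step 4: sensitivity to the assumed 10%.** If recently screened people return kits at 25% in both arms, unadjusted power is 73.7%, 63.9% and 53.1% at r = 10, 20 and 30%. If they never return one, it is 75.8%, 68.9% and 61.3%, and the relative risk stays at 1.50.

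**Step 5: precision of the interaction.** At r = 20% there are 180 and 45 participants per arm in the two groups. The standard error of the difference between their risk differences is √(0.4219/180 + 0.18/45) = 0.0796. The 95% half-width is 1.96 × 0.0796 = 15.6 points, around an assumed true difference of 12.5. The interaction describes; it does not test with useful power.

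**The case against.** The strongest reply is that naming covariates and subgroups belongs in the SAP, which is not shown, and that the article need not list them. That is fair as far as an omission goes. However, the article does state the two rules at issue, adjustment conditional on imbalance and moderation conditional on efficacy. Those can be criticised as written.

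Other parts of the defence stand and limit the point:

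- **Eligibility.** A reader might infer that the lack of a recent-testing window is a design error. Study aims defines the population as Native American youth and young adults in the community, and under-use of services is background, not an inclusion target. The average effect among sexually experienced volunteers is a legitimate question.
- **Baseline screening ignored.** A reader might infer this too. It goes too far: adjustment is possible, exploratory moderation is planned after a positive result, and past STI infection is named as a mediator in the hypotheses.
- **Dilution.** The documents give neither the share recently screened nor any evidence that the effect is smaller in them. The 20–25% is stated for the control group as a whole. If it and the relative risk already average over recently screened people, there is no further loss.
- **Measurement.** A survey report of earlier screening is not the same measure as returning a study kit, and the article does not say that the survey dates the last test.

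**Conclusion.** The point holds as a small, inexpensive improvement. The plan collects baseline screening but makes its use depend on observed imbalance and on a positive result. After a null result, no planned analysis would show whether the effect differs by prior screening. Randomisation is expected to balance prior screening, so the issue is precision and interpretation, not bias between arms.

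The size is modest. Under the assumptions in steps 2 and 3, fixed adjustment adds about 1 to 2 points of power at r = 10 to 30%. It would add less if recently screened people return kits at much the same rate as others.

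It would be wrong to conclude that the change restores the power lost in the dilution scenario. At r = 20%, power goes from 66.7% to 68.4%, still well below 81.8%, and that loss is itself hypothetical. The main benefit is a clearer reading of a null or weak result.

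**What to change.** 1. In Statistical analysis, make the primary comparison adjusted for baseline self-reported STI screening, whatever balance is observed. Use the item as the existing survey records it, with recency if that is available. The log-binomial model already named can serve.
2. In the same section, report the treatment-by-prior-screening interaction as exploratory whatever the primary result, with the distribution of prior screening by arm.
3. In Study aims, add prior screening to the variables to be explored.

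Leave eligibility as it is.

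The cost is a few lines of analysis text. Self-reported screening carries recall error, and the interaction estimate will be imprecise (step 5). Recruitment began on April 1, 2019, so a recency question added later would be missing for those already enrolled. This is why the existing item should be the default.

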### Participant randomization and study sample size

This study is at RCT. The randomization sequence is computer generated and used to randomize individuals to one of two study groups: intervention or control. A stratified randomization technique will be used to ensure equivalent 1:1 allocation of study conditions across three gender groups (male/trans male; female/trans female and other, which includes those who identify as two-spirited, bi-gendered, crossdresser, genderqueer, or for whom none of these options apply), and three age groups (i.e. 14–17, 18–21, and 22–26). Within each age/gender strata, participants will be randomized in blocks of 4 to ensure equal allocation to intervention and control groups. Participants, but not study staff or investigators, will be blinded to study group participation.

The primary outcome is completion of self-administered STI screening between the baseline and 3-month study visit. Based on prior research, we estimate that 20–25% of the control group will complete STI screening [12]. We anticipate POFG will increase STI screening by at least 50% (i.e. relative risk of 1.5 comparing the proportion completing STI screening in the intervention group to the control group). Given these assumptions, retention rates from past RCTs conducted by the study team within the target population, a two-sided alpha of 0.05 and 80% power, we will enroll a total of 450 participants (225 in each arm) to sufficiently power the trial.

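### A single block size of 4 within strata, with study staff unblinded, could make up to a third of allocations predictable if those who screen or recruit can see earlier assignments

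*Protocol article*

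**What the plan says.** All statements are in the Protocol article.

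- **Sequence** (Participant randomization and study sample size): "The randomization sequence is computer generated and used to randomize individuals to one of two study groups: intervention or control".
- **Stratification** (same section): "A stratified randomization technique will be used to ensure equivalent 1:1 allocation of study conditions across three gender groups", crossed with "three age groups (i.e. 14–17, 18–21, and 22–26" years. Three by three gives nine strata.
- **Blocks** (same section): "Within each age/gender strata, participants will be randomized in blocks of 4 to ensure equal allocation to intervention and control groups". No other block size is mentioned.
- **Blinding** (same section): "Participants, but not study staff or investigators, will be blinded to study group participation".
- **Size** (same section): "we will enroll a total of 450 participants (225 in each arm) to sufficiently power the trial".
- **Screening** (Participant recruitment and informed consent): "Study staff will screen potential participants for eligibility criteria".
- **Recruitment** (same section): a non-probability sample, obtained by "posting flyers in public and conducting in-person recruitment at community gathering locations".

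Under Statistical analysis, the primary outcome is the return of a self-administered test by the 3-month visit. It is compared by a chi-square test, or by log-binomial regression if baseline characteristics differ between arms.

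**The concern.** Each of these choices alone is tolerable; the combination is the difficulty. In a 1:1 block of 4, anyone who knows the block size and the assignments already made in that block can often work out the next one. A screener has to establish age, and gender group is easily learned, so the stratum can be known before enrolment. Staff who are not blinded may know what was assigned before. In-person convenience recruitment leaves some discretion over whom to approach and when.

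The outcome is voluntary: the participant returns a kit or does not. Willingness to test is something a recruiter might sense in conversation. If more willing people tended, even without intent, to be enrolled when the next slot was known to be intervention, the arms would differ in that trait from the start. The primary test is unadjusted unless measured baseline characteristics differ, so a difference in an unmeasured trait would pass into the result.

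**Working it through.** The article gives no figure for predictability, so there is none to reproduce. The calculation rests on two stated inputs: block size 4 and 1:1 allocation, hence two intervention and two control places per block.

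**1. One complete block.** There are six equally likely orders: AABB, ABAB, ABBA, BBAA, BABA, BAAB. In two of the six the first two assignments match. Take an observer who knows the block size and every earlier assignment in the stratum.

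| Position | Probability it is certain | Probability the best guess is right |
|---|---|---|
| 1 | 0 | 1/2 |
| 2 | 0 | 2/3 |
| 3 | 1/3 | 1/3 × 1 + 2/3 × 1/2 = 2/3 |
| 4 | 1 | 1 |

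- Certain in advance: (0 + 0 + 1/3 + 1)/4 = 33.3%.
- Best guess right: (1/2 + 2/3 + 2/3 + 1)/4 = 70.8%, against 50% by chance.

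**2. The whole trial.** A complete block contributes 4/3 certain allocations on average. An incomplete last block contributes 1/3 if it has three members and 0 if it has one or two. The split of the 450 across strata is not given, so two splits are assumed:

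- 50 in each of nine strata: 12 complete blocks each, 12 × 4/3 = 16, and 9 × 16 = 144, or 32% of 450.
- Strata of 100, 100, 60, 60, 60, 60, 4, 3 and 3: 66.7 + 80 + 1.3 + 0.7 = 148.7, or 33%.

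So about 144 to 149 of 450 allocations are open to such an observer.

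**3. What steering could do (illustration; the amount of steering is assumed).** Suppose that on the certain third of slots, people enrolled to intervention are 5 percentage points more likely to test than average, and those enrolled to control 5 points less likely. The bias in the difference is 1/3 × 10 = 3.3 points. At 2 points each way it is 1/3 × 4 = 1.3 points. The planned difference at a relative risk of 1.5 is 10 points (20% v 30%) to 12.5 points (25% v 37.5%).

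With no true effect, a 22.5% rate and 225 per arm, the standard error is √(2 × 0.225 × 0.775/225) = 0.0394. A 3.3-point bias is 0.0333/0.0394 = 0.85 standard errors. The two-sided rejection rate is then P(Z > 1.11) + P(Z < −2.81), about 0.13 to 0.14 instead of 0.05.

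**4. After changing the block sizes.** This was simulated with 50 per stratum and 400 runs, for an observer who knows which sizes are possible but not which is in use.

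| Scheme | Certain, actual sizes unknown | Certain, block boundaries known |
|---|---|---|
| Fixed 4 | 32% (incomplete last blocks included) | 33.3% |
| 4 and 6 | about 5% | (4 × 1/3 + 6 × 1/4)/10 = 28% |
| 4, 6 and 8 | about 2% | (4 × 1/3 + 6 × 1/4 + 8 × 1/5)/18 = 25% |

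The gain therefore depends on recruiters not learning where blocks begin and end.

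**The case against.** A reader might infer that the design does make a third of allocations predictable, that the same people recruit and know the assignments, and that the primary comparison is therefore biased beyond repair. The documents do not support that.

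- **One third is a ceiling.** It needs an observer who follows every earlier assignment in each of nine strata. Nothing says any recruiter holds such a tally, and several recruiters working in parallel would lower the figure.
- **The roles are not identified.** The term study staff is used both for those who screen and for those who are unblinded, but the text does not say they are the same individuals. It does not name who recruits in person, or say that recruiters are told the block size. The size is known only in that the article states it.
- **Discretion is limited.** Some participants respond to flyers, and eligible, interested people go on to consent. No latitude to defer or decline them is described.
- **Some detection and adjustment is possible.** STI screening intention is a listed outcome and the surveys are completed at baseline as well as at follow-up, so a proxy for willingness may be available.
- **Concealment may be handled elsewhere.** How the list is held and when an assignment is released are matters for the full protocol, which is not shown.

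All five points stand, and they make the finding conditional. They do not remove it. Concealing the list gives no protection against deduction from a known block size and visible past assignments. Intention is also only a partial measure of willingness, so adjusting for it would leave some bias.

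**Conclusion.** The finding holds as a conditional weakness. A single block size of 4 within nine strata, with unblinded study staff, exposes up to 33.3% of allocations to certain prediction and allows a best guess that is right up to 70.8% of the time. This assumes that someone who screens or recruits knows the block size and sees the earlier assignments in the stratum. The arithmetic is exact under that assumption; how far it is met cannot be told from the article.

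Selection on willingness to test is a risk and has not been shown to occur. The bias of 1.3 to 3.3 points rests on assumed steering on every predictable slot and shows scale only; it is not an estimate. Missing detail on concealment or release timing is no part of the finding. The change is still worth making, because it replaces a stated method with a less predictable one at little cost.

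**What to change.** **For any remaining enrolment**

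- Generate the rest of the list with randomly varied block sizes within strata, for example 4 and 6, and do not disclose the sizes to recruiting staff.
- Keep the stratum's assignment history from those who screen and recruit. This matters at least as much as the block sizes, since varied blocks help little once the boundaries are known.

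**If enrolment is complete**

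- Report who recruited and screened, and what they could see of earlier assignments and the block size.
- Identify the predictable allocations from the list (the fourth in each block, and the third where the first two match). Compare baseline screening intention between arms among them, provided it was recorded before the quiz. With about 144 to 149 such allocations in all, a null result would be weak reassurance.

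**Cost.** A new computer-generated list, possible notification of the review boards and tribal bodies that approved the design (recruitment began on April 1, 2019), and slightly more possible imbalance in sparse strata, probably those in the third gender group.

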### Control condition

The control program includes: a) a brief self-assessment (also called ‘quiz’), b) quiz score, and c) personalized messaging. For the control condition, the quiz, score and messaging will pertain to consumption of water, soda and sugar sweetened beverages. There will not be a comparable clinical prediction tool in the quiz for the control condition. However, based on the answers given on the control quiz, key steps the control participant can take to meet the recommended daily intake of water and sugar sweetened beverages will be delivered. The control quiz with resulting score and personalized messaging will take approximately ten minutes to complete and will be delivered via tablet at the first study visit. Control participants will also be offered a self-administered, non-clinic based STI testing kit (for *Neisseria gonorrhea*, *Chlamydia trachomatis* and *Trichomonas vaginalis*) after receiving their personalized messages. The content and structure of the control condition was recommended by the local study team from the participating tribal community and endorsed as a beneficial comparison to the intervention.

The quality of both programs (intervention and control) will be ensured through self-administration via tablet. Thus, delivery of each quiz and corresponding messaging is standardized across participants in each group.

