### STI treatment

For participants who opt to take the STI testing kit (intervention or control) they can: 1) complete it and return it to a study staff immediately, 2) take the test with them, complete it at a later time and drop it off at the designated study office, or 3) complete it at a later time and coordinate with a study staff to have it picked up at a location they choose.

All participants (intervention and control) who test positive for a STI will receive an assisted referral to a Public Health Nurse at IHS with whom we have partnered on this study to ensure all participants who test positive for one or more STIs receive timely and high-quality treatment.

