### Statistical analysis

Study hypotheses will be tested using an “intent to treat” analysis. Baseline characteristics will be compared between groups using chi-square tests for binary or categorical outcomes, and Wilcoxon rank-sum tests for continuous outcomes. For the primary outcome of STI screening uptake, the proportion of participants completing screening (i.e. returning a test to study staff) by the 3-month study visit will be compared across groups using a chi-square test or log-binomial regression if participant characteristics are found to vary at baseline between groups. For all analyses, participants who drop-out during the study and don’t provide at least 3-month follow-up data will be removed from the analysis. If at 3- or 6-months follow-up the POFG intervention shows efficacy for increasing STI screening uptake, we will conduct mediation and moderation analyses to explore what factors may be impacting the efficacy of POFG to change STI screening behavior.

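### Study staff who know the arm also receive and pick up the kits that make up the primary outcome, so unequal staff effort could enter that outcome unseen

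*Protocol article*

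**What the plan says.** Four statements in the Methods of the protocol article bear on this point.

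- **Blinding** (Participant randomization and study sample size): "Participants, but not study staff or investigators, will be blinded to study group participation".
- **Endpoint** (Statistical analysis): the proportion completing screening, explained as "returning a test to study staff) by the 3-month study visit will be compared across groups using a chi-square test".
- **Return routes** (STI treatment), open to both arms: "complete it and return it to a study staff immediately"; "take the test with them, complete it at a later time and drop it off at the designated study office"; or "complete it at a later time and coordinate with a study staff to have it picked up at a location they choose".
- **Standardisation** (Control condition): "The quality of both programs (intervention and control) will be ensured through self-administration via tablet", from which the article concludes that "delivery of each quiz and corresponding messaging is standardized across participants in each group".

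The kit comes at the same point in both arms, after the personalised messages. For the control arm: "Control participants will also be offered a self-administered, non-clinic based STI testing kit". The Intervention section says the same for the intervention arm (POFG). Neither section says who makes the offer.

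**The concern.** The primary outcome is a behaviour that ends with study staff, and those staff are not masked. The stated hypothesis is that the intervention arm will screen more. If that expectation leads, even unintentionally, to more prompting or more flexible pick-up in one arm, the extra kits count as successes in the primary comparison.

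The analysis could not correct for this. Staff effort would differ along the same line as the allocation, so the chi-square test or log-binomial model would attribute it to the quiz and messages. The claim of standardised delivery rests on tablet self-administration and so covers what the tablet delivers, not how kits are retrieved. The limitations in the Discussion name self-report bias and the inability to separate the intervention's components, but not staff knowledge of the arm.

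The described delivery does not appear to need unmasked staff. Both programmes take about ten minutes, run on a tablet at the first visit, and lead to the same kit.

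**Working it through.** **Where staff enter the endpoint**

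| Step | Described as | Staff involved? |
|---|---|---|
| Quiz and messages | Self-administered on tablet, both arms | No, standardised |
| Kit offer | Passive wording, both arms | Not stated |
| Immediate return | Handed to staff | Yes |
| Later drop-off | Left at the study office | At receipt |
| Later pick-up | Arranged with staff | Yes |
| Endpoint | Test returned to study staff | Yes |

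Two of the three return routes need direct dealings with staff, and the third ends at their office.

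**Inputs for the illustration**

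- From the document: 225 per arm, two-sided alpha 0.05, control return rate 20–25%.
- Assumed: no true programme effect, and unequal effort that converts a fraction c of intervention-arm non-returners. The document gives no value for c.

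**Formulas.** With control rate p, the intervention rate is q = p + c(1 − p), the difference is b = q − p, and m = (p + q)/2.

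- SE under the null: s0 = √[2m(1 − m)/n]
- SE at the assumed rates: s1 = √[(p(1 − p) + q(1 − q))/n]
- Rejection probability: 1 − Φ[(1.96·s0 − b)/s1] + Φ[(−1.96·s0 − b)/s1]

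**No difference in effort** (c = 0): rejection is 5.0%, the nominal level.

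**p = 0.25, c = 5%:**

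- q = 0.25 + 0.05 × 0.75 = 0.2875, so b = 0.0375 and RR = 0.2875/0.25 = 1.15.
- s0 = 0.0418, 1.96·s0 = 0.0819, s1 = 0.0418.
- Upper tail: (0.0819 − 0.0375)/0.0418 ≈ 1.06, giving 14.4%. Lower tail: 0.2%. Total about 14.6%.
- A simulation of 100,000 trials gives 14.8%.

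**p = 0.25, c = 10%:**

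- q = 0.25 + 0.10 × 0.75 = 0.325, so b = 0.075 and RR = 1.30.
- s0 = 0.0427, 1.96·s0 = 0.0836, s1 = 0.0425.
- Upper tail: (0.0836 − 0.075)/0.0425 ≈ 0.20, giving 42.0%. Lower tail: negligible.
- The simulation gives 42.1%.

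**In kits.** The two scenarios amount to 0.0375 × 225 ≈ 8 and 0.075 × 225 ≈ 17 extra returned kits. The smallest observed difference that reaches significance is about 7.9 points with a control rate of 20% and 8.5 points with 25%, or roughly 18–20 kits out of 225.

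**Sensitivity**

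| n per arm | Control rate | c = 5% | c = 10% |
|---|---|---|---|
| 225 | 20% | 17.6% | 51.1% |
| 225 | 25% | 14.6% | 42.0% |
| 191 | 20% | 15.6% | 44.8% |
| 191 | 25% | 13.1% | 36.6% |

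The lower rows assume 15% loss (225 × 0.85 ≈ 191), because the plan drops participants without 3-month data. The document gives no loss figure. The pattern does not depend on the exact n.

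**The case against.** Much of the case on the other side stands.

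- **The outcome is objective.** A kit is returned or it is not. This guards well against misclassification, but not against unequal effort in getting the kit returned.
- **The arms are nominally treated alike.** Both get the same kit at the same stage, the same three return options and the same referral if positive. That is a real safeguard, although it fixes what is available to participants and not how actively staff pursue it.
- **Return is largely driven by the participant.** The participant chooses the route and the pick-up location. The article describes no reminders and no chasing by staff.
- **The article is condensed.** An offer script, a contact rule or restricted REDCap permissions may stand in the full protocol or a manual. Their absence from the article is not a fault. The point rests on the explicit statement that staff are not blinded; if such safeguards exist, citing them would answer much of it.
- **Unmasked staff are common in behavioural trials**, and the article discloses the choice. It is neither an error nor a contradiction.
- **The effort difference is invented.** Any assumed bias inflates rejection. The figures show how sensitive the endpoint is, not what will happen here. Even the 10% scenario at a 25% control rate gives RR 1.30, below the planned 1.5.

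A reader might go further and infer that unmasked staff make the kit offer, that the same people handle every step, or that staff chase returns in one arm. The document states none of these. Staff receipt and arranged pick-up are explicit, and they are enough for the point.

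**Conclusion.** The point holds as a performance-bias risk created by a stated design choice. Staff know the arm, kits are returned through staff, and that return is the primary outcome. Unequal prompting or retrieval would therefore pass into the endpoint and be read as programme effect.

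Its size is unknown. With 25% in both arms and 225 per arm, converting 5% or 10% of intervention-arm non-returners gives about 15% or 42% rejection with no true effect. These figures depend on assumed conversion rates and full retention. It would be wrong to infer from them that a positive result would be spurious or that staff will treat the arms differently, because nothing in the document shows a difference in effort. The change is worth making because it is cheap, not because the design is invalid.

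**What to change.** For participants still to be enrolled:

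1. Have the tablet or REDCap assign the arm and branch to the matching quiz. Hide the arm from staff who collect or pick up kits and from whoever records the outcome.
2. Present the kit offer on screen in identical words in both arms.
3. Apply one rule on contacts about kit return to both arms, and log contacts by arm so that equal effort can be shown. The rule and log can also cover enrolled participants still within their 3-month window.
4. Amend the blinding sentence to say which staff are masked and from what date. Recruitment opened on April 1, 2019, so masking must not be claimed for all participants.

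**Cost:** a change to REDCap branching and permissions, one on-screen text and a contact log. It needs no extra staff and no change to sample size, endpoint or care.

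**Downside:** masking may leak if a participant mentions the quiz topic, and it does not reach those already enrolled. The contact log is therefore needed even if masking works well.
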